# Magnetic resonance Adenosine perfusion imaging as Gatekeeper of invasive coronary intervention (MAGnet): study protocol for a randomized controlled trial

**DOI:** 10.1186/s13063-017-2101-6

**Published:** 2017-07-28

**Keywords:** Stable coronary artery disease, Cardiac magnetic resonance imaging, Coronary angiography, Myocardial revascularization, Outcomes and prognosis, Quality of life

## Abstract

**Background:**

Current guidelines for the diagnosis and management of patients with stable coronary artery disease (CAD) recommend functional stress testing for risk stratification prior to revascularization procedures. Cardiac magnetic resonance imaging (CMR) is a modality of choice for stress testing because of its capability to detect myocardial ischemia sensitively and specifically. Nevertheless, evidence from randomized trials evaluating a CMR-based management of stable CAD patients in comparison to a more common angiography-based approach still is limited.

**Methods/design:**

Patients presenting themselves with symptoms indicating a stable CAD and a class I or IIa indication for diagnostic coronary angiography are prospectively screened and enrolled in the study. All subjects receive a basic cardiological work-up and guideline-directed medical therapy. A 1:1 randomization in two groups is being performed. Patients in group 1 undergo diagnostic coronary angiography and subsequent revascularization according to current guidelines. Subjects in group 2 undergo adenosine stress CMR and in case of myocardial ischemia are sent to coronary angiography. Follow-up is planned for 3 years. During this time, the number of primary endpoints (defined as cardiac death and non-fatal myocardial infarction) and unplanned invasive procedures will be documented. Furthermore, symptom burden and quality of life will be assessed by use of the Seattle Angina Questionnaire. Sample size is calculated to prove non-inferiority of the CMR-based approach.

**Discussion:**

In case this study is able to accomplish its aim to prove non-inferiority of the CMR-based management in patients with stable CAD; the importance of this emerging modality may further increase.

**Trial registration:**

ClinicalTrials.gov, identifier: NCT02580851. Registered on 14 October 2015. Unique Protocol ID: 237/11

**Electronic supplementary material:**

The online version of this article (doi:10.1186/s13063-017-2101-6) contains supplementary material, which is available to authorized users.

## Background

Current guidelines for the diagnosis and management of patients with stable coronary artery disease (CAD) recommend – besides thorough history and physical examination – proper risk stratification and non-invasive detection of myocardial ischemia prior to invasive therapy [1, 2]. The detection or exclusion of moderate to severe reversible myocardial ischemia is a crucial part of the work-up process. When ischemia is present, patients are designated to a high-risk group with a high probability of having a prognostic benefit from revascularization procedures [3–5]. Patients without ischemia do not seem to benefit from revascularization over optimal medical therapy, at least with regard to prognosis [6]. This emphasizes the need for functional testing prior to therapeutic decisions.

Adenosine perfusion cardiac magnetic resonance imaging (CMR) is an imaging modality which is able to reliably detect reversible myocardial ischemia and thus plays an increasing role in the diagnosis and risk stratification of patients with suspected or known CAD [7–11]. Though CMR, therefore, is highly recommended in the diagnostic work-up of stable CAD patients, there is only one study evaluating a CMR-driven approach in patient management with regard to the occurrence of major cardiac events [12].

Invasive coronary angiography still is considered to be the “gold-standard” for the diagnosis of CAD, though it exhibits several limitations and shortcomings. Multiple studies have documented the significant interobserver variability in the grading of coronary artery stenosis, as well as the frequent occurrence of under- and overestimation of hemodynamic relevance [13, 14]. One has to conclude that coronary angiography may provide anatomical information but is not the modality of choice concerning the detection of myocardial ischemia. This is of special interest, as there is a reported frequency of complications due to diagnostic coronary angiographies of about 1.5% [15]. Nevertheless, coronary angiography remains the most often performed diagnostic test in the setting of stable CAD, with more than one half of elective percutaneous coronary interventions (PCI) done without previous stress testing [16].

The objective of our study is to show that a CMR-based conservative or invasive management of patients with suspected or known CAD is not inferior with regard to major cardiac endpoints and quality of life in comparison to a – more conventional – coronary angiography-based approach. We assume that a significant number of diagnostic coronary angiographies and PCI could be spared without decrease in patient safety and comfort. Therefore, we designed this single-center, open-label, randomized controlled trial to test for non-inferiority of the two diagnostic groups.

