### Follow-up

Adherence will be achieved by regular contact between the study personal and the participants. Follow-up information is gathered on a yearly basis after enrollment by outpatient clinic visits and by telephone interviews of patients and their general practitioners. Any reported adverse event will be reported and its significance evaluated by the investigators. At this time point, interim analyses will be performed by the investigators. The study will be stopped by the investigators if a safety concern arises that prohibits the continuation of the trial.

The primary endpoint is defined as cardiac death (defined as in [25]) and non-fatal myocardial infarction according to the current universal definition [26]. Any diagnostic or interventional coronary procedure that has not been scheduled at the time of the initial diagnostic work-up will be recorded as an unplanned procedure. Symptom burden and quality of life are assessed by SAQ each year. A follow-up period of 3 years is planned for each patient. Standardized follow-up forms have been established and are available at our institution. If consent is withdrawn by a participant, the data that has already been collected will be removed from further analysis.

Figure 1 shows the study schedule according to the populated SPIRIT figure.

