### Sample size prediction/statistics

It has been shown that the annual event rate for the defined primary endpoint is 6.3% in case of a pathological and 1.0% in case of a normal CMR examination [27]. Retrospective analysis of our data revealed a 30% rate of pathological CMR examinations during the last years, thus the expected annual event rate would be 2.59% for the whole primary CMR group. In patients primarily undergoing coronary angiography, pooled annual event rates have been shown to be about 6% [6, 28]. For the sample size prediction, a Fisher’s exact test with a power of 80% and a *p* value indicating significance of < .05 was used. The study was designed to prove non-inferiority with a defined non-inferiority margin of 1% within a 3-year follow-up period. This lead to a predicted sample size of 90 participants per group. Taking dropout rate and safety margin into account, we plan to enroll 100 patients into each group. Annual interim analyses will be performed to evaluate the need for further enrollment in case of insufficient event rates for an appropriate statistical analysis.

The following statistical tests will be used after completion of follow-up: to test the relationship between categorical classification factors, the chi-squared test will be applied. Continuous variables will be tested for normal distribution by the D’Agostino-Pearson test. In case of a normal distribution, variables will be reported as mean ± standard deviation and a two-tailed *t* test will be applied for comparison. Variables without normal distribution will be reported as median with percentiles and the Mann-Whitney rank-sum test will be used for comparison. As mentioned above, Fisher’s exact test will be applied to test for non-inferiority of the event rates of both groups. Overall, a *p* value ≤ .05 will be judged significant.

Data management will only be carried out by trained personal. The database is stored on protected servers of the academic hospital.

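### The objective claims non-inferiority for quality of life, but the only margin and non-inferiority test are for event rates, so similar SAQ scores could not establish it

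*Protocol article*

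**What the plan says.** The objective, at the end of the Background section, covers two outcomes: CMR-based management "is not inferior with regard to major cardiac endpoints and quality of life" compared with the angiography-based approach. The same paragraph derives the design from that aim, describing a "randomized controlled trial to test for non-inferiority of the two diagnostic groups".

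Under Follow-up, the primary endpoint is cardiac death and non-fatal myocardial infarction. For the other outcome that section says: "Symptom burden and quality of life are assessed by SAQ each year".

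The section Sample size prediction/statistics states one margin: "The study was designed to prove non-inferiority with a defined non-inferiority margin of 1% within a 3-year follow-up period". The calculation around it uses event rates only. The non-inferiority analysis is likewise confined to events: Fisher's "exact test will be applied to test for non-inferiority of the event rates of both groups".

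That section does not name the SAQ. It does give a general rule for continuous variables. If they are normally distributed, "variables will be reported as mean ± standard deviation and a two-tailed *t* test will be applied for comparison". Otherwise: "Variables without normal distribution will be reported as median with percentiles and the Mann-Whitney rank-sum test will be used for comparison". The common threshold is that a p "value ≤ .05 will be judged significant".

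**The concern.** The objective and the analysis do not match. A t test or Mann-Whitney test asks whether the groups differ. A non-inferiority claim needs a stated amount of harm and evidence that the true difference is smaller than that amount. For quality of life the article gives no such amount and no rule for judging it.

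If the two groups report similar SAQ scores, which is what a non-inferiority objective anticipates, the planned test returns a p-value above .05. That result does not separate a truly negligible difference from one the trial was too imprecise to see. The investigators would then have an objective they could neither confirm nor reject by any rule in the article.

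The outcome is not trivial here. The Background expects procedures to be spared with no loss of patient comfort, and the Discussion presents symptom burden and quality of life as part of what this trial adds.

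**Working it through.** **1. Setting the sections side by side**

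| Element | Events | Quality of life (SAQ) |
|---|---|---|
| In the non-inferiority objective (Background) | yes | yes |
| Margin | 1% within 3 years | none |
| Non-inferiority test | Fisher's exact test | none |
| Test that applies | as above | t test or Mann-Whitney, by the general rule for continuous variables |
| Enters the sample size | yes | no |

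The plan has no SAQ figure to reproduce. Its sample-size inputs are all event rates. The CMR-arm rate follows from them: 0.30 × 6.3% + 0.70 × 1.0% = 1.89% + 0.70% = 2.59% per year. The resulting 90 per group is used below only as an arm size. Whether 90 is right for the event endpoint is a separate question on which nothing here depends.

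**2. How often would a real deficit be non-significant?**

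Inputs:
- n = 90 per arm, the predicted sample size before the allowance that raises enrolment to 100.
- Two-sided significance level 0.05, from the statistics section.
- Standard deviation (SD) of 15, 20 or 25 SAQ points: assumed, not in the document.
- True deficit d of 5, 8 or 10 points in the CMR group: assumed, not in the document.

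Formulas (normal approximation to the t test):
- SE = SD × √(2/n)
- P(non-significant) = Φ(1.96 − d/SE) − Φ(−1.96 − d/SE)
- Half-width of the 95% confidence interval = 1.96 × SE

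Worked case, SD 20 and d = 5: SE = 20 × √(2/90) = 2.98; d/SE = 1.68; Φ(0.28) − Φ(−3.64) = 0.61.

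| SD | SE | Half-width | d = 5 | d = 8 | d = 10 |
|---|---|---|---|---|---|
| 15 | 2.24 | 4.4 | 39% | 5% | 1% |
| 20 | 2.98 | 5.8 | 61% | 24% | 8% |
| 25 | 3.73 | 7.3 | 73% | 43% | 24% |

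With all 100 per arm analysed, the 5-point column becomes 35%, 58% and 71%. A valid non-inferiority test whose margin equalled the deficit would accept it in only 2.5% of trials (5% if run one-sided at 0.05).

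**3. Could this sample support an SAQ margin?**

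Take a true difference of zero, one-sided 0.025 and 80% power. The number per arm is 2 × SD² × (1.96 + 0.84)² / margin².

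| Margin | SD 15 | SD 20 | SD 25 |
|---|---|---|---|
| 5 points | 142 | 252 | 393 |
| 8 points | 56 | 99 | 154 |
| 10 points | 36 | 63 | 99 |

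So 90 per arm falls short for a 5-point margin at every SD tried. For a 10-point margin it is enough at SD 15 and 20, and just short at SD 25.

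**The case against.** The strongest reply is that quality of life is only an accompanying outcome. The Abstract and the Discussion both mention it as an addition to the clinical endpoints, Follow-up restricts the primary endpoint to death and infarction, and the non-inferiority test is explicitly about events. On this view one phrase in the Background overreaches, and the SAQ analysis belongs to a fuller protocol or analysis plan. Much of this stands. The choice of SAQ scale and time point can indeed be left to such a document, and its absence is not an error here. But the article is not silent on analysis. It lists the tests to be used and reserves the non-inferiority test for event rates. A plan that followed this section could not deliver the objective in the Background, so one of the two has to change.

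A second reply is that the SAQ is placed under the difference tests only by inference, and that only the t test is called two-tailed. That is correct. The Mann-Whitney test is still a test of difference, whichever its sidedness, and no other rule is offered.

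A third is that the protocol has a safeguard: CMR-group patients whose symptoms progress or stay insufficiently controlled are also evaluated for an invasive approach. This may make a quality-of-life deficit less likely. It does not supply a way of showing that there is none.

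**Conclusion.** The mismatch is real. The Background claims non-inferiority for quality of life, while the statistics section provides a margin and a non-inferiority test for events alone. When SAQ scores are similar there is no valid route to the claim. This concerns a non-primary outcome and leaves the event comparison untouched.

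Three stronger readings are tempting, and the document does not support them:
- **That the plan will treat p > .05 as non-inferiority.** The article never says so. A reader might infer it because no other rule is given.
- **That no result could support the objective.** A significant difference favouring CMR would. It is the non-significant result that cannot.
- **That the trial is too small for a quality-of-life claim.** That depends on an SD and a margin the document does not give. With a wide margin and a small SD, 90 per arm could suffice.

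The percentages illustrate size and are not properties of this trial. Over the assumed SDs of 15 to 25 points and deficits of 5 to 10 points, the chance of missing a real deficit runs from 1% to 73%. The mismatch itself rests on no assumed number.

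**What to change.** **Preferred.** Remove quality of life from the non-inferiority objective in the Background. In the statistics section, state that the between-group SAQ difference will be reported with its 95% confidence interval as a secondary, descriptive result, and that p > .05 will not be read as non-inferiority. The cost is two or three sentences and a weaker quality-of-life claim. No new data are needed.

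**If the claim is to be kept.** Prespecify one SAQ scale, one time point and a justified margin in SAQ points, and conclude non-inferiority only if the 95% confidence interval excludes that margin. Two cautions apply:
- The trial is open-label and recruiting, and the investigators run yearly interim analyses. The margin must therefore be set, and documented as set, without sight of comparative SAQ data.
- Precision may be too low for a narrow margin. With a half-width of about 4.4 to 7.3 points (90 per arm, assumed SD 15 to 25), a 5-point margin would not be excluded at SD 20 or 25 even with an observed difference of zero.

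Either change can go through the route for protocol modifications that the article already describes under General information.

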## Methods/design

### General information

This study has been approved by the local Ethics Committee of our university (Ethikkommission der Universität Ulm, Chairman [name]. [name], reference number 237/11, Additional file 1). It has been partially funded by Guerbet Germany, Sulzbach, Germany (see Additional file 2 for funding contract). The funder does not have any influence concerning study design, data collection, analysis and the decision to submit the report. Other financial expenses and the involved personal are provided by our own institution.

As our study is an investigator-initiated, single-center trial (academic hospital, Germany) there is no coordinating center or steering committee. Patient enrollment, endpoint adjudication and data management will be carried out by the authors of this protocol independently from the sponsor. To monitor the conduction of the trial, the members of the Investigator Committee meet on a regular basis and exceptionally when concerns arise.

Participants are covered by the academic hospital in case harm should occur in the context of this trial. Provisions are not intended.

The study is registered at ClinicalTrials.gov (identifier: NCT02580851). Protocol modification will be communicated to the ethics committee and will be documented at ClinicalTrials.gov. The adapted Standard Protocol Items: Recommendations for Interventional Trials (SPIRIT) Checklist is attached as Additional file 3.

After completion of the trial, publication of the results is intended in a peer-reviewed scientific journal. Publication will only be carried by the authors of this manuscript without the help of professional writers. Granting full access to the protocol or participant-level dataset is not intended.

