### Patient recruitment

Generally, informed consent will be obtained by the investigators after personal elucidation from all participants prior to enrollment in the study. All patients presenting themselves in the outpatient clinic of our university hospital for the evaluation of symptoms indicating a stable CAD (e.g., exercise-related angina pectoris or dyspnea) will be screened prospectively. Patients at intermediate to high risk (according to recommended risk scores) and a class I or IIa indication for diagnostic coronary angiography (Additional file 4: Table S1) will be considered eligible unless they exhibit the following exclusion criteria: unstable angina pectoris, cardiac or respiratory instability, contraindication for CMR examination [17], known allergy to gadolinium-based contrast agents, impaired renal function (glomerular filtration rate <30 ml/min), contraindication or allergy to adenosine, pregnancy, age below18 years and inability to give written informed consent. It is irrelevant whether a CAD has already been diagnosed at the time of first presentation.

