### Protocol

All patients receive thorough history-taking, physical examination and a basic cardiological work-up including rest electrocardiogram, treadmill testing and echocardiography. Further prediagnostics (e.g., stress-echocardiography) is allowed and the respective results will be documented. According to general recommendations, risk stratification scores for each individual are calculated [18, 19]. In order to assess symptom burden and quality of life, the standardized Seattle Angina Questionnaire (SAQ) is carried out in each subject [20, 21]. All patients receive guideline-directed medical therapy (GDMT) [1].

Patients are randomized in two groups in a 1:1 fashion (blocked computer-generated random numbers). The allocation sequence is only available to a designated study nurse who will be phoned in case of an allocation. The trial is designed in an open-label fashion, i.e., there is no blinding after the initial allocation.

In group 1, patients directly undergo diagnostic coronary angiography. A PCI is performed according to current guidelines in case of ≥70% stenosis in a coronary vessel with ≥2-mm diameter [1, 2] or hemodynamically relevant stenoses in fractional flow reserve (FFR) testing.

Subjects in group 2 initially receive adenosine perfusion CMR for functional testing. The examination is conducted on a 3.0-Tesla whole-body scanner with a 32-channel phased-array cardiac receiver coil according to a well-established standard protocol [22–24]. In case reversible ischemia can be detected, subjects are sent to coronary angiography and PCI afterwards. Additional file 5: Figure S1 provides the study flowchart.

In case of progressive or insufficient symptom control, patients of group 2 (CMR group) are also evaluated for an invasive therapeutic approach. The following procedures will be documented.

There are no other diagnostic or therapeutic interventions planned or prohibited in the setting of this trial.

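### Cardiac death and infarction are classified without masking by the protocol authors; with about 25 expected events this can matter near the margin, and masking the classification is cheap

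*Protocol article*

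**What the plan says.** Under General information the article assigns the work as follows: "Patient enrollment, endpoint adjudication and data management will be carried out by the authors of this protocol". The same sentence adds that they act independently of the sponsor; it claims no independence from treatment allocation. As a single-centre trial, "there is no coordinating center or steering committee".

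Patient recruitment adds that "informed consent will be obtained by the investigators". The Protocol section states: "The trial is designed in an open-label fashion, i.e., there is no blinding after the initial allocation". The only person described as holding the allocation sequence is a designated study nurse.

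The Follow-up section says "The primary endpoint is defined as cardiac death" and adds non-fatal myocardial infarction. It cites a published definition for the first and the universal definition for the second. Information is collected yearly by "outpatient clinic visits and by telephone interviews of patients and their general practitioners", with standardized forms. On the yearly looks it says: "At this time point, interim analyses will be performed by the investigators". The investigators also evaluate adverse events and decide on stopping for safety.

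**The concern.** Patients and treating physicians cannot be masked to CMR versus angiography. The people who classify events largely can be, and the article does not provide for it. Since it names the adjudicators and rules out blinding after allocation, this is a stated feature of the design and not a detail left to a fuller document.

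The endpoint is not all-cause death. Someone must decide whether a death was cardiac and whether a clinical episode meets the infarction definition, sometimes from a telephone account. The groups also differ in the procedures they undergo, so knowing the group can colour how an equivocal record is read. The authors state an aim of showing that CMR is not inferior. The direction of any resulting bias is unknown. With few events and a narrow margin, a small difference between groups in classification could matter to the primary conclusion.

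**Working it through.** **Inputs**, all from Sample size prediction/statistics:
- Annual event rate, CMR group: 2.59%. This reproduces: 0.30 × 6.3% + 0.70 × 1.0% = 1.89% + 0.70% = 2.59%.
- Annual event rate, angiography group: about 6%.
- Patients per group: 90 calculated, 100 planned. Both are taken as stated; how the 90 was derived is a separate question.
- Margin: 1% over 3 years, read here as absolute percentage points.
- Significance level: 0.05, sidedness not stated.

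**Step 1, expected events over 3 years.**
- CMR: 1 − (1 − 0.0259)³ = 7.57%, or 7.6 events per 100.
- Angiography: 1 − (1 − 0.06)³ = 16.94%, or 16.9 events per 100.
- Together about 25 events. The expected difference, CMR minus angiography, is 7.57 − 16.94 = −9.37 points.

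**Step 2, weight of one event.** Reclassifying one event in one group shifts the risk difference by 1/100 = 1.00 point at 100 per group, or 1/90 = 1.11 points at 90 per group.

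**Step 3, effect on the conclusion.** Non-inferiority turns on a confidence limit or a test, not on the point estimate. The article names Fisher's exact test and gives no interval rule, so a simple Wald limit serves as illustration:

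upper limit = (p_CMR − p_angio) + z × √[p_CMR(1 − p_CMR)/n + p_angio(1 − p_angio)/n]

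with z = 1.96 for a two-sided 95% limit and 1.645 for a one-sided 95% limit.

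For 17 vs 8 at n = 100 the standard error is √(0.17 × 0.83/100 + 0.08 × 0.92/100) = 0.04634, and −0.0900 + 1.96 × 0.04634 = +0.0008, i.e. +0.08 points. That starting point and all four one-event changes from it are below (limits in points, margin +1):

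| Angiography vs CMR events | Difference | Upper limit, two-sided 95% | Upper limit, one-sided 95% |
|---|---|---|---|
| 17 vs 8 | −9.0 | +0.08 (met) | −1.38 (met) |
| 17 vs 9 | −8.0 | +1.26 (not met) | −0.23 (met) |
| 17 vs 7 | −10.0 | −1.10 (met) | −2.53 (met) |
| 16 vs 8 | −8.0 | +0.94 (met) | −0.50 (met) |
| 18 vs 8 | −10.0 | −0.78 (met) | −2.26 (met) |

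One of the four changes crosses the margin with the two-sided 95% limit, and none with the one-sided 95% limit. With the one-sided limit it takes three added CMR events: 17 vs 10 gives +0.91 (met) and 17 vs 11 gives +2.04 (not met).

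At 90 per group, 15 vs 7 gives +0.59 (met) and 15 vs 8 gives +1.91 (not met) two-sided; one-sided the values are −0.93 and +0.35, both met.

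**Step 4, reading of the margin.** If 1% per year was meant, the 3-year margin is 3 points. One event is then a third of it, and 17 vs 9 (+1.26) meets it even two-sided.

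**The case against.** Four stronger readings are tempting, and the documents do not carry them.

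- **One reclassified event decides the trial.** A reader might infer this because one event equals the margin in size. But one event is 1 point in any trial with 100 per group. The expected difference lies about 10 points inside the margin (1 − (−9.37) = 10.37), and Step 3 shows that most one-event changes leave the conclusion as it was. The change that crosses the margin from 17 vs 8 adds a CMR event, which runs against the authors' hypothesis, although from 17 vs 9 removing one would flip the result the other way. The fragility comes mainly from the narrow margin and small sample, which masking would not cure. Nothing in the documents says how often misclassification would occur.
- **The same person enrols and adjudicates a given patient.** The article gives these tasks to the authors as a group. A division of labour is neither described nor excluded.
- **Adjudicators see results by group every year.** The statistics section gives the purpose of the interim looks as judging whether event numbers call for more enrolment. It does not say that results are tabulated by group. The investigators' power to stop for safety makes this plausible but not certain.
- **The endpoint is left to free judgement.** It is not: both components have cited definitions, and there are yearly contacts and standardized forms.

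What survives is that these safeguards narrow discretion without removing it, and that none of them masks the classifier. Independence from the sponsor addresses a different source of bias.

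**Conclusion.** The point holds in a limited form. Primary events are classified by the protocol authors, who as a group also enrol patients and manage the data. The yearly interim analyses fall to the investigators, on a natural reading the same group. No masking to treatment group is provided at any stage.

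The size of the problem is one full point of risk difference per reclassified event at 100 per group. That can reverse the conclusion when the result lies near the boundary, where the plan's own expected counts place it under a two-sided 95% limit. It does not do so generally, and not at those counts under a one-sided 95% limit.

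This rests on an absolute 3-year margin of 1 point, event rates as the plan assumes, and a Wald limit as the yardstick. The amount and direction of any misclassification are unknown. I rate masking as a cheap improvement to the credibility of the primary result, not as a defect that invalidates the design.

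**What to change.** Amend the adjudication sentence under General information along these lines:

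> For each suspected primary event, the study nurse who holds the allocation sequence prepares a dossier from which group assignment and CMR results have been removed. Procedural information needed to classify a peri-procedural infarction is kept. An investigator not involved in that patient's care classifies the event by the cited definitions, masked to group and before any interim summary by group is produced. Where available, a second such investigator reviews the classification.

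The procedural details have to stay in, because an infarction around an intervention cannot be classified without them. One masked classifier, with a second where available, is asked for because the article does not say how many investigators there are, so a larger panel cannot be assumed.

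Recruitment was ongoing at submission, so the change can still be made, and events already recorded can be reviewed again from redacted dossiers. Treatment, endpoint definitions and sample size stay as they are.

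The cost is redaction work by existing staff: about 25 expected events, plus suspected events that are not confirmed, whose number the article does not give. The downside is that masking will be imperfect at a single centre, especially for peri-procedural events, where the retained details may reveal the group.
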